## Abstract

**Background:**

Heart failure(HF) and atrial fibrillation(AF) frequently coexist in the same patient and are associated with increased mortality and frequent hospitalizations. As the concomitance of AF and HF is often associated with a poor prognosis, the prompt treatment of AF in HF patients may significantly improve outcome.

**Methods/design:**

Recent implantable cardiac resynchronization (CRT) devices allow electrical therapies to treat AF automatically. TRADE-HF (trial registration: NCT00345592; http://www.clinicaltrials.gov) is a prospective, randomized, double arm study aimed at demonstrating the efficacy of an automatic, device-based therapy for treatment of atrial tachycardia and fibrillation(AT/AF) in patients indicated for CRT. The study compares automatic electrical therapy to a traditional more usual treatment of AT/AF: the goal is to demonstrate a reduction in a combined endpoint of unplanned hospitalizations for cardiac reasons, death from cardiovascular causes or permanent AF when using automatic atrial therapy as compared to the traditional approach involving hospitalization for symptoms and in-hospital treatment of AT/AF.

**Discussion:**

CRT pacemaker with the additional ability to convert AF as well as ventricular arrhythmias may play a simultaneous role in rhythm control and HF treatment. The value of the systematic implantation of CRT ICDs with the capacity to deliver atrial therapy in HF patients at risk of AF has not yet been explored. The TRADE-HF study will assess in CRT patients whether a strategy based on automatic management of atrial arrhythmias might be a valuable option to reduce the number of hospital admission and to reduce the progression the arrhythmia to a permanent form.

**Trial registration:**

NCT00345592

## Background

Heart failure (HF) and atrial fibrillation (AF) are two of the major diseases affecting older adults and, when chronic, are often associated with increased mortality, frequent hospitalizations and decreased quality of life [1-3]. These two disorders share similar characteristics and frequently coexist in the same patient, with the prevalence of AF increasing together with the severity of HF [4-7]. The association of AF with a worse prognosis in HF patients is still under debate with controversial results in favor [2,5,8] or against [9,10]. Even though data regarding improved survival rates is currently lacking, as far as health care is concerned, one goal of AF treatment in HF patients is to reduce hospitalization and improve quality of life [11]. The recent introduction of an implantable device which can provide both cardiac resynchronization therapy (CRT) and ventricular and atrial electrical therapies, paves the way toward the combined treatment of both diseases. In fact, CRT has proven to be effective in correcting asynchrony in HF [12-14], while defibrillation therapy has demonstrated its effectiveness in treating both ventricular and atrial arrhythmias [15-17]. Due to the high prevalence of AF in HF patients who meet indications for an implantable cardioverter defibrillator (ICD) [18,19], this combined therapy could treat HF, prevent sudden cardiac death, prevent AF and restore sinus rhythm when necessary. As AF may compromise the efficacy of CRT in terms of reverse remodeling [20,21] a break in the AF/HF cycle could improve prognosis both by optimizing HF treatment and restoring sinus rhythm. The TRADE-HF study has been designed to assess the benefits of an automatic, device-based management of atrial arrhythmias in patients suffering from symptomatic HF, indicated for CRT treatment with defibrillation backup and implanted with a dual (atrial and ventricular) defibrillator.

## Methods/Design

### Study Design and Objectives

The TRADE-HF is a prospective, open-label, randomized, multi-center, two parallel arm study. The study has been approved by the local Ethic Committees of all 20 participating centers and has been registered to http://www.clinicaltrials.gov site (NCT00345592). Enrollment started in November 2006. The steering committee of the study is responsible for the study design and its amendments.

Primary objective of the TRADE-HF study is to demonstrate a reduction in the combination of hospitalizations for cardiovascular causes or death for cardiovascular causes or development of permanent AF, using a device-based treatment of atrial arrhythmias (i.e. automatic therapy) compared to a traditional approach including hospitalization for symptoms and and/or in-hospital treatment of AT/AF (i.e. traditional therapy). Automatic therapy implies that atrial arrhythmias are detected by the device itself which treats the rhythm automatically within 3 hours after episode onset with a predetermined sequence of programmed electrical therapies (anti-tachycardia pacing and electrical shock). On the other side in the traditional arm automatic shock therapy is not active; therefore, patients who will experience symptomatic atrial arrhythmias at home will refer to their center, where treatment of the atrial arrhythmia will be done according to center's practice (e.g. drugs, external cardioversion, device shock commanded by the physician in a hospital environment). Hospitalizations for cardiovascular causes will include any unplanned cardiac cause hospitalization including day hospital, access to the emergency units and in-hospital procedures of AT/AF cardioversion. Permanent AF is considered as any form of AF that is found to be refractory to drug or electrical therapy, for which the physician resigns to take additional actions to restore sinus rhythm and that persists additionally for at least one month. After obtaining informed consent, a three-month observation period ensues, during which the device parameters are optimized, data on atrial arrhythmias are collected and patient's response to the device treatment is assessed. Thereafter, patients are randomized to the two different treatment arms, automatic and traditional therapy in a 1:1 ratio. After being randomized, patients are followed for three years to assess endpoints. The study flowchart is shown in figure 1.

**Figure 1 F1:**
[figure not shown]
**Study flowchart**. RND: Randomization.

Secondary objectives include: the performance assessment of automatic atrial therapies, and a comparison between the automatic-managed and traditional therapy arm of the following outcomes: in-hospital costs, Quality of Life (QoL) scores, number of hospital admissions and the separate components of the primary endpoint.

An exploratory analysis will be done in order to investigate the response to CRT treatment for the enrolled patients. A positive response to CRT is considered a relative LVEF increase ≥ 20% and/or a relative LVESV decrease ≤ 15% measured at echocardiographic recording associated with a functional assessment defined as reduction of at least one NYHA class or of 15 points at Minnesota living with heart failure score for NYHA class III patients or at least stable NYHA class or 10 points decrease at Minnesota living with heart failure score for NYHA class II patients. This definition reflects patient's cardiac remodeling associated to a functional improvement in highly symptomatic patients or at least a stable functional condition in mild symptomatic patients. The proportion of CRT responders will be analyzed at time of randomization and one year after randomization; additionally a correlation, separately at the two time points, will be searched among the proportion of CRT responders, the burden of atrial fibrillation (total percentage of recorded AT/AF episodes: 0; <10%; >10%) and the target site of left ventricular lead (lateral wall vs. other).

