### Data Analysis

Descriptive statistics will be presented for the collected variables, overall and according to the randomization group; for categorical variables absolute and relative frequencies; for continuous variables mean, standard deviation, median, 25th-75th percentile, minimum and maximum. Baseline characteristics of the two study arms will be listed. Cox modeling will be used to perform the primary analysis and assess the association between treatment (traditional vs. device-managed) and the primary endpoint. Hazard ratios and their 95% confidence intervals will be presented together with Kaplan-Meier cumulative survival and with event rates (per 100 persons per year) in each group. The model will include the following potential confounders: evidence of AT/AF in the patient's medical history or recorded by the device before randomization and patients' response to CRT at randomization. In particular, group effects will be tested by interaction terms comparing the treatment effect in patients who are or are not responders to CRT at randomization. Competing events (causes of death other than cardiovascular, transplant or ventricular assist device implant) will be censored at the time they occur. The primary analysis will be done according to Intention to treat (ITT) i.e. automatic shocks programmed according to randomization. Survival analysis techniques will be used to evaluate time-to-event for the evolution to chronic AF and for both subgroup analyses (CRT responders and AT/AF). In case the primary endpoint is fulfilled, additional post-hoc analyses will be performed. In particular a positive response to CRT responsiveness will be analyzed with respect to the planned variables by means of a logistic regression model. The device's ability to manage and correctly classify atrial arrhythmia will be evaluated considering the sensitivity, specificity and accuracy of the device's classification compared to that made by the Event Committee. Quality of life scores, number and total duration of hospital admissions (for all causes, cardiac causes and for heart failure), total duration of AF and total costs will be compared between the two study arms after 3 years using the appropriate statistical test, according to distribution. For economic analysis costs are estimated for hospitalization (reasons, entry date, duration, department), interventions and instrumental examinations performed. A P value of at least 0.05 will be used for statistical significance.

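### The LVESV part of the CRT-responder definition has its inequality reversed, so responder status in the Cox model covariate, interaction test and subgroup contradicts its stated aim

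*Protocol article*

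**What the plan says.** Under Study Design and Objectives, in the paragraph on the exploratory CRT-response analysis, the protocol article gives its only definition of a positive response. It has two parts, and both are required.

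- **Echo part:** a relative LVEF rise of at least 20% and/or "a relative LVESV decrease ≤ 15% measured at echocardiographic recording".
- **Functional part:** in NYHA class III, "reduction of at least one NYHA class or of 15 points at Minnesota living with heart failure score for NYHA class III patients"; in class II, "at least stable NYHA class or 10 points decrease at Minnesota living with heart failure score for NYHA class II patients".

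The sentence after the definition gives its purpose: "This definition reflects patient's cardiac remodeling associated to a functional improvement in highly symptomatic patients", or at least a stable condition in those with milder symptoms. The proportion of responders is to be analysed at randomization and one year later.

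The variable is used again under Data Analysis. The Cox model for the primary endpoint adjusts for AT/AF in the history or "recorded by the device before randomization and patients' response to CRT at randomization". It also carries a test of effect modification: "group effects will be tested by interaction terms comparing the treatment effect in patients who are or are not responders to CRT at randomization". CRT responders are one of two named subgroups. A logistic regression of response is listed among post-hoc analyses that depend on the primary endpoint being met.

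**The concern.** The two limbs of the echo part point in opposite directions. The LVEF limb sets a floor, so a larger improvement qualifies. The LVESV limb sets a ceiling, so a smaller improvement qualifies and a larger one does not. A definition meant to reflect remodelling cannot exclude patients because their ventricular volume fell too much.

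The definition is introduced as exploratory, but Data Analysis puts the same variable into the primary model. A program coded faithfully from the text would place some patients with almost no echo change among the responders, and some with a large volume reduction among the non-responders. The comparison of treatment effect between responders and non-responders would then not answer the question it is meant to answer.

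**Working it through.** **1. No stated figure depends on the definition.** The article gives no expected responder proportion to reproduce. The sample size rests on 60% versus 43%, two-sided alpha 0.05 and 90% power. The two-proportion formula gives, per group,

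n = [1.960·√(2·0.515·0.485) + 1.282·√(0.60·0.40 + 0.43·0.57)]² / 0.17² ≈ 5.19 / 0.0289 ≈ 179.5, rounded up to 180.

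This is 360 in total, as stated. Responder status does not enter, so the sign error leaves it unchanged.

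**2. The echo rule evaluated case by case.** Take LVEF rise below 20%, so that only the LVESV limb decides:

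| Relative LVESV change | As written (decrease ≤ 15%) | Sign turned (decrease ≥ 15%) |
|---|---|---|
| 10% increase | fails, or passes if a negative decrease is counted | fails |
| no change | passes | fails |
| 5% fall | passes | fails |
| 15% fall | passes | passes |
| 16% fall | fails | passes |
| 30% fall | fails | passes |
| 40% fall | fails | passes |

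Among these patients, the two rules agree on a fall only at exactly 15%. With an LVEF rise of 20% or more, every patient passes under either rule.

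**3. Adding the functional part.** Take two NYHA class II patients, both stable in class. One has a 1% LVESV fall and no LVEF change: echo passed, function passed, responder. The other has a 40% LVESV fall and a 15% LVEF rise: echo failed, non-responder. In class III the functional part is stricter, so fewer patients without remodelling become responders. A large LVESV fall with an LVEF rise under 20% still fails.

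**4. Size on the echo part.** The article gives no distributions. Assume a bivariate normal with mean LVESV fall 15% (SD 20), mean relative LVEF rise 20% (SD 25) and correlation 0.7. Both thresholds then lie at their means, so quadrant probabilities have a closed form:

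- P(LVEF rise < 20% and LVESV fall > 15%) = 1/4 − arcsin(0.7)/(2π) = 0.250 − 0.123 = 0.127. These fail as written and pass when corrected.
- P(LVEF rise < 20% and LVESV fall < 15%) = 0.250 + 0.123 = 0.373. These pass as written if LVESV increases count, and fail when corrected.

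If increases count, misclassification is 0.127 + 0.373 = 0.50. The share passing the echo part is 1 − 0.127 = 87% as written, against 1 − 0.373 = 63% corrected.

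If only true decreases count, patients with LVEF rise < 20% and an LVESV increase (0.199 by simulation) fail under both rules. Misclassification is then 0.50 − 0.20 = 0.30.

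**5. Size for final responder status.** A patient who fails the functional part is a non-responder under either sign. Final misclassification is therefore the echo figure times the functional pass rate among those patients. Assume 50–70% pass, independently of echo change:

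- 0.30 × 0.50 = 15% to 0.30 × 0.70 = 21%;
- 0.50 × 0.50 = 25% to 0.50 × 0.70 = 35%.

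**The case against.** The strongest reply is that the intent is plain. The purpose is stated in the next sentence, and the symbol is probably a slip for ≥ 15% or for a signed change of ≤ −15%. An analyst might well notice, and the full protocol behind this condensed article may carry the right sign. That lowers the chance that the literal rule is ever programmed. It does not make the printed rule right: this is a stated threshold in the wrong direction, not a detail left to another document.

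Three further objections stand and limit the point.

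- **The echo part is only half of the definition.** A patient without remodelling is not automatically a responder, so the echo-only percentages overstate the error in the variable that enters the model.
- **The 50% figure needs a strained reading,** in which an LVESV increase counts as a decrease of at most 15%. On the ordinary meaning of decrease, the 30% figure applies.
- **Not every patient is affected.** Those with an LVEF rise of 20% or more are classified the same under either sign. To say that all the planned analyses contrast the wrong patients would go too far.

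A reader might also infer that the primary result is compromised, because the variable is in the primary Cox model. The article does not support this. Response for the model is assessed by the randomization visit, before the arms diverge, so misclassification should be balanced between them.

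**Conclusion.** The definition is wrong as written: its LVESV limb contradicts the paired LVEF limb and the stated aim. This follows from the text alone and needs no assumption.

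The consequence is a distorted CRT-response covariate, treatment-by-response interaction, responder subgroup and responder proportions at both time points. Errors run both ways, with non-remodelled patients let in and remodelled patients shut out. The logistic regression is affected too, but it is post hoc and conditional, so it adds little weight. The error does not by itself bias the randomized treatment comparison.

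The percentages (30%, or 50% on the wider reading, for the echo part; 15–21% or 25–35% for final status) are illustrations. They depend on the assumed means, SDs, correlation and independent functional pass rate, none of which the article gives. In NYHA class II, where stability suffices, the reduction from the functional part would be small. The error should be corrected, but it is not one on which the trial's main conclusion turns.

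**What to change.** In the responder definition, change the LVESV limb to a relative decrease of ≥ 15%, or equivalently a signed relative change of ≤ −15%. Either form also settles that an LVESV increase does not qualify. Apply the same rule at randomization and at one year, and make the correction in writing before responder status is derived, so that it cannot look like a data-driven change to a variable in the primary model.

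The cost is one symbol in the text and in any derivation program. No new data are needed: Interventions and Follow Up already provides for echocardiography at enrollment, at the randomization visit and at one year.

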
Early treatment of AF also seems to be justified as far as histopathology is concerned, as arrhythmia is not only an electrical pathology, but a condition that, over an extended time, may induce non-reversible organic diseases such as fibrosis and conduction abnormalities [34-37]. In light of this, early AF treatment could be reserved even for those patients with a lower AF burden or for those with no history of AF. A recent work by Saxon et al. reports that 25% of CRT candidates with a history of AF, experience recurrent AF within 6 months of implant [38]. Given the high prevalence of AF in patients currently indicated to CRT, and the opportunity to treat new onset AF promptly, the inclusion criteria of the TRADE HF study consider all patients implanted with a biventricular device with defibrillator, regardless of their atrial arrhythmic history.

Finally, whether CRT may have an effect on AF burden in patients with persistent or paroxysmal AF is still a matter of research and prospective studies to evaluate this impact have been encouraged [33]. It is not known whether reverse remodeling, induced by biventricular pacing in patients who respond to CRT, may have an effect on the incidence of AT/AF: minimal data exist on the effect of long term CRT on left atrial dimensions and/or LV reverse remodelling in patients with AF and the results are contradictory [8,31,39] even if a recent. The TRADE HF study will analyze if there are substantial differences in the incidence and characteristics of atrial fibrillation between CRT responders and non-responders.

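### The exploratory one-year analysis of CRT response against AF burden does not list randomized arm, although the randomized therapy is expected to change AF burden

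*Protocol article*

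**What the plan says.** Study Design and Objectives (text after Figure 1) states the aim: "An exploratory analysis will be done in order to investigate the response to CRT treatment for the enrolled patients". It sets two time points: "The proportion of CRT responders will be analyzed at time of randomization and one year after randomization". It then names what will be related: "a correlation, separately at the two time points, will be searched among the proportion of CRT responders, the burden of atrial fibrillation" (categories 0, below 10%, above 10%) "and the target site of left ventricular lead (lateral wall vs. other". Response combines an echocardiographic criterion with a functional one based on NYHA class or the Minnesota score.

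Data Analysis adds that "a positive response to CRT responsiveness will be analyzed with respect to the planned variables by means of a logistic regression model". This comes directly after a condition: "In case the primary endpoint is fulfilled, additional post-hoc analyses will be performed". Arm is not mentioned for this model. It is mentioned for the Cox model of the primary endpoint, which contains treatment and an interaction with response at randomization.

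On the therapy, Study Design and Objectives says that the device in the automatic arm "treats the rhythm automatically within 3 hours after episode onset". In the traditional arm the automatic shock is off, and symptomatic patients go to their center. The Discussion expects automatic therapy possibly to shorten AF and reduce later arrhythmias. Data Analysis compares total AF duration between arms as an outcome. The Discussion states the question: the study "will analyze if there are substantial differences in the incidence and characteristics of atrial fibrillation between CRT responders and non-responders".

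**The concern.** At randomization, burden has been recorded before allocation, so its association with response owes nothing to arm. At one year burden has been exposed to the randomized therapy, and the article itself treats AF duration as an outcome of that therapy.

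Arm may also influence response. NYHA class and the Minnesota score are assessed with patients and investigators aware of the arm (Interventions and Follow Up). The same section group anticipates that some patients will leave automatic therapy because of shock discomfort, which could affect quality of life independently of burden. If arm acts on both variables, it is a common cause of them, and an analysis without arm can show an association that exists in neither arm. Separately, if automatic therapy keeps burden low whatever the CRT response, a link that is real in the traditional arm is diluted when the arms are combined.

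At stake is how the one-year result is read on the Discussion's question about AF in responders and non-responders.

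**Working it through.** The plan gives no figure for this analysis. The one planned number borrowed below is 180 per group. It reproduces from the two-proportion formula with 60% vs 43%, two-sided 0.05 and 90% power: [1.96·√(2·0.515·0.485) + 1.2816·√(0.60·0.40 + 0.43·0.57)]² / 0.17² = 179.5, so 180.

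All burden and response rates below are assumptions. Arms are equal in size (1:1 in the plan). OR is the odds ratio of response for high against lower burden.

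**A. Arm affects response other than through burden; no link within either arm (within-arm OR 1.0).** AF patients only, burden >10% against the rest.

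- Case 1: burden >10% in 40% (traditional) and 10% (automatic); response 55% and 65%.
  - High: (0.40·0.55 + 0.10·0.65)/0.50 = 0.570
  - Lower: (0.60·0.55 + 0.90·0.65)/1.50 = 0.610
  - Combined OR = (0.570/0.430)/(0.610/0.390) = 0.85
- Case 2: burden >10% in 50% and 10%; response 50% and 65%.
  - High: (0.50·0.50 + 0.10·0.65)/0.60 = 0.525
  - Lower: (0.50·0.50 + 0.90·0.65)/1.40 = 0.596
  - Combined OR = 0.75

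**B. Same mechanism, all patients, burden >10% against 0.** Response is 60% in the traditional arm; automatic therapy cuts the >10% share by a fraction d; the zero-burden group is equal in both arms. With r the response in the automatic arm, response at high burden is (0.60 + (1−d)·r)/(2−d), and at zero burden (0.60 + r)/2. AF prevalence cancels.

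| d | r | Combined OR |
|---|---|---|
| 0.5 | 0.65 | 0.97 |
| 0.5 | 0.70 | 0.93 |
| 0.9 | 0.65 | 0.92 |
| 0.9 | 0.70 | 0.84 |
| 0.5 or 0.9 | 0.60 | 1.00 |

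The last row shows the condition: with no other effect of arm on response there is no distortion.

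**C. Arm affects response only through burden, with the same link in both arms.** A true OR of 0.30 stays 0.30 when the arms are combined, and 0.50 stays 0.50.

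**D. The link differs by arm; arm has no effect on response.** AF patients, 60% responders in both arms. Burden >10% in 30% of responders and 50% of non-responders (traditional): OR = (0.30/0.70)/(0.50/0.50) = 0.43. In the automatic arm 10% and 10%: OR 1.0. Combined, 20% against 30%: OR = (0.20/0.80)/(0.30/0.70) = 0.58. This describes neither arm. A single arm-adjusted OR would also be an average of the two, so a by-arm table is needed to see it.

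**Numbers available.** With 180 per arm, the plan's 35% with any AT/AF (a three-year figure, so generous at one year) and the Case 1 shares, patients with burden >10% number 180·0.35·0.40 ≈ 25 (traditional) and 180·0.35·0.10 ≈ 6 (automatic). For the Case 1 combined OR, the standard error of log OR is √(1/18.0 + 1/13.5 + 1/57.6 + 1/36.9) ≈ 0.42, giving an approximate 95% interval of 0.4 to 1.9.

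**The case against.** The strongest reply is that this is a condensed article. The text does not say that the arms will be combined, nor does it rule out analysis by arm, and covariates of an exploratory model are often left to a fuller document. That stands in part: combining the arms is an inference from the enrolled-patient population and the variable list. But the article does enumerate the variables here, and it names treatment explicitly for the Cox model, so arm is absent from a stated list.

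Second, bias is conditional. An effect of arm on response that runs through AF control is mediation, and working steps B and C confirm that it leaves the odds ratio intact when the link is the same in both arms. This stands. The other route depends largely on the unblinded functional criterion, and response also requires an echocardiographic change, which limits how far that route can carry.

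Third, a reader might infer that the therapy determines burden. The documents do not support that. The Discussion says only that it may shorten or reduce AF; about 35% of patients are expected to have any episode in three years, so most have zero burden in either arm; crossover is allowed; and the traditional arm is required to have the automatic shock off, with nothing said there about automatic pacing therapy.

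Fourth, in these illustrations the distortion is small against sampling error, and an arm-by-burden interaction would rest on about 6 high-burden patients in the automatic arm. Both stand.

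**Conclusion.** The one-year analysis should account for arm. Its listed variables omit arm, while the article expects the randomized therapy to alter one of them and leaves part of the other open to unblinded assessment. The size depends on assumptions: a within-arm odds ratio of 1.0 appears as roughly 0.75 to 0.97 if arm affects response by another route, and a link present in only one arm is diluted (0.43 becomes 0.58 in the example). If neither condition holds, nothing is distorted.

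A reader might go further and infer that the analysis cannot answer the Discussion's question. That is not supported. The question is worded descriptively, the randomization time point is sound, survival analyses for the responder subgroup are also planned, and arm can be added to the one-year analysis. Severity is low: the analysis is labelled exploratory, the logistic model is post-hoc and conditional, and the primary and secondary comparisons are untouched.

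**What to change.** In Study Design and Objectives and in Data Analysis:

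- Name randomized arm as a covariate in the one-year model of CRT response.
- Tabulate the one-year burden-response association by arm, descriptively, with counts.
- State that the one-year result is an association that does not settle whether burden affects response or response affects burden; adjustment for arm does not resolve that.
- Keep the unadjusted analysis for the randomization time point.
- Leave an arm-by-burden interaction optional, because few automatic-arm patients are likely to have burden above 10%.

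No new data are needed. The cost is one covariate, one table and slightly less precision; the by-arm estimates will be imprecise in the automatic arm and should be presented as such.

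### AF burden is defined as a percentage of episodes with no usable denominator and no class for exactly 10%, and the 3-year AF comparison uses a raw total duration despite unequal follow-up (minor)

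*Protocol article*

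**What the plan says.** Two AF measures appear in the protocol article, both under Methods/Design.

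- **Burden classes.** The exploratory paragraph of Study Design and Objectives (after the Figure 1 caption) opens: "An exploratory analysis will be done in order to investigate the response to CRT treatment for the enrolled patients". On timing it says: "The proportion of CRT responders will be analyzed at time of randomization and one year after randomization". It continues: "additionally a correlation, separately at the two time points, will be searched among the proportion of CRT responders", the AF burden and the site of the left ventricular lead. Burden is given as "the burden of atrial fibrillation (total percentage of recorded AT/AF episodes: 0; <10%; >10" (percent). No denominator is named.
- **Total duration.** Data Analysis says that "total duration of AF and total costs will be compared between the two study arms after 3 years", using a test chosen by distribution. No monitored-time denominator is attached.

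Three other statements bear on the point. Before randomization, "a three-month observation period ensues, during which the device parameters are optimized, data on atrial arrhythmias are collected". After it, the automatic arm's device "treats the rhythm automatically within 3 hours after episode onset", while "in the traditional arm automatic shock therapy is not active". The Sample Size section assumes 15% attrition from loss to follow-up or failure to adhere to the design.

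**The concern.** Burden normally means how much of the time a patient spends in AT/AF. The printed unit is episodes, and a patient's recorded AT/AF episodes are by definition all AT/AF episodes. A 10% cut-off on that quantity has no meaning, so an analyst has to guess what was intended. The class limits also leave one value unassigned.

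The second measure, a raw sum of AF time, does have a clear unit. However, it grows with the time a patient is observed. In a trial where cardiovascular death is part of the primary endpoint and some loss to follow-up is expected, a patient who dies or leaves early gets a low total whatever the rhythm was.

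At stake are the interpretability of an exploratory explanatory variable and the fairness of a between-arm comparison of AF duration. If the choice of metric is left until the data are in, it can also become data-driven.

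**Working it through.** The plan states no figure for either measure, so there is none to reproduce.

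**1. Is the percentage computable?** Take the printed unit literally, within a patient: AT/AF episodes ÷ recorded AT/AF episodes. This is 100% for anyone with at least one episode and 0/0 for anyone with none. Values such as 3% or 12% cannot occur. AT/AF as a share of all device-recorded arrhythmia episodes would be computable, but the text does not name that denominator, and it would not measure exposure to AF. A 10% limit makes sense for time in AT/AF ÷ monitored time.

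**2. Do the classes form a partition?** Apply the rules x = 0; x < 10; x > 10:

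| x (%) | Classes met |
|---|---|
| 0 | 0 and <10% |
| 0.1 | <10% |
| 9.9 | <10% |
| 10 | none |
| 10.1 | >10% |
| 100 | >10% |

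The gap at 10% is real. The overlap at 0 is only literal: with a separate class 0, the next class reads naturally as >0 to <10%.

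**3. Does the choice of unit matter?** The episode patterns here are assumed, over 365 days (8,760 h).

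- One 60-day episode: 60/365 = 16.4% of time, 1 episode.
- Twenty 3-hour episodes: 20 × 3 = 60 h; 60/8,760 = 0.7% of time, 20 episodes.

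Time and count order these two patients oppositely. This shows why the unit must be stated. It does not show that the trial would use counts.

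**4. How does the raw total depend on follow-up?** Assume a constant 10% of time in AF.

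- Total = 0.10 × 365.25 × years observed.
- Followed 3 years: 0.10 × 365.25 × 3 = 109.6 days.
- Death at 1 year: 0.10 × 365.25 × 1 = 36.5 days.
- As a percentage of monitored time, both are 10%.

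**5. What does this do between arms?** With the same 10% burden in both arms, the difference in mean totals is 36.5 days × the difference in mean follow-up in years. The documents give no figure for that difference, so a range is assumed: 0 years gives 0 days, 0.1 years gives 3.7 days and 0.3 years gives 11.0 days. The arm with shorter follow-up appears to have less AF.

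**The case against.** The best defence is that the wording is loose shorthand. A variable called burden, in percent and cut at 10%, is most sensibly read as percent of time in recorded AT/AF episodes. On that reading patients are ordered correctly, and a gap at exactly 10% touches almost nobody. Windows and the handling of death or loss are also details that an article may leave to the full protocol or analysis plan.

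Much of this stands, and it limits the point. A reader might infer that patients are ranked wrongly. The documents do not support that: misranking needs an episode-count reading, which the text nowhere establishes. A reader might also infer that the classes depend on treatment arm. At the randomization time point no arm has been assigned. At one year a time-based burden could also differ by arm, because automatic therapy may shorten episodes, so arm dependence is not specific to the wording. The exploratory paragraph does not plan a between-arm comparison of the classes.

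It does not dispose of the point, because the article does more than stay silent. It prints a unit and class limits that cannot be applied as written, and it names a raw total as the quantity to compare. Choosing a test by distribution does not correct an outcome that scales with follow-up. The censoring rule in Data Analysis is given for competing events and does not adjust a sum of AF time. It is fair to add that the 110 versus 37 days is a patient-level effect. Bias between arms also requires follow-up to differ between them, which the documents do not show. The 15% attrition includes non-adherence, so not all of it shortens follow-up.

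**Conclusion.** The point holds, as a minor one. The burden variable, as printed, has no meaningful denominator and leaves exactly 10% without a class. The 3-year comparison uses a total that mixes AF with length of observation: at a constant 10% of time in AF, about 110 days over 3 years against about 37 days with death at 1 year. These figures rest on the assumed constant 10%. Any bias between arms rests further on unequal follow-up between them.

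The reach is limited. The burden classes serve an exploratory correlation and, as one of the planned variables, a post-hoc logistic model of CRT response that is run only if the primary endpoint is met. Total AF duration is one of several additional between-arm comparisons. The primary endpoint and the sample size do not use either measure. The primary Cox model adjusts for evidence of AT/AF before randomization, not for the burden classes.

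**What to change.** - **Burden.** Define it as cumulative device-recorded AT/AF time divided by device-monitored time, as a percentage. Use the observation period as the window for the randomization time point, and randomization to one year for the one-year time point.
- **Classes.** Use 0; >0 to <10%; ≥10%. Placing 10% in the lower class would serve equally well, provided it is fixed in advance.
- **3-year comparison.** Compare AT/AF time as a percentage of monitored time between arms, in place of the raw total. This removes the mechanical link with follow-up. It does not remove any real association between AF and death, so monitored time should be reported by arm beside it.

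The cost is wording only, settled before the data are analysed. Episodes are already recorded by the device and total AF duration is already planned. The one added requirement is monitored time per patient, which is assumed to be available from device and follow-up dates. Sample size and visits do not change.
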